## Sample size

Expected difference in HTC-uptake between study-arms (1^st^ primary outcome): 80% (door-to-door) versus 65% (pitso)

k= 0.1

Power: 80%; Significance level: 5%

clients per cluster: 200 (persons attending the services per cluster)

According to formula of Hayes & Benett^[[2]](#footnote-2)^: 6 clusters per arm

## COLLECTED VARIABLES AND THEIR ANALYSIS

### Variables collected during testing-campaigns

| Variable | Type of variable |
| --- | --- |
| Age | Continuous |
| Sex | Binomial |
| Weight (kg) | Continuous |
| Height (cm) | Continuous |
| Accepts HIV-test (Y/N) | Binomial |
| 1^st^ time tester (Y/N/missing) | Binomial |
| Test result (Pos/Neg/Intermediate) | Categorical |
| Enrolled on pre-ART or ART within 1 month (Y/N) | Binomial |
| Absolute CD4-count the day tested positive | Continuous |
| Clinical WHO-stage the day tested positive | Ordinal |
| TB-screening (Pos/Neg/Missing) | Binomial |
| Blood-Pressure in mmHg | Continuous |
| Blood-Glucose in mmol/l | Continuous |
| Uptake of deworming and Vitamin A (Y/N) | Binomial |
| Updated immunization schedule (Y/N) | Binomial |
| Catch-up vaccination provided (Y/N) | Binomial |
| Uptake of contraception among eligible women (Y/N) | Binomial |
| Type of contraception provided | Categorical |

### Variables collected 5 weeks after the campaign

| Variable | Type of variable |
| --- | --- |
| Enrolled into chronic care for HIV (Y/N) | Binomial |
| Enrolled on ART (Y/N) | Binomial |
| Brought sputum to facility within ≤ 5 days (Y/N) | Binomial |
| Result of sputum examination (Pos/Neg) | Binomial |
| Absolute number tested HIV-positive during this period from the 5 villages with campaigns and from 5 control villages (without campaign) | Count |

### Collection and processing of data

During the testing campaign, data will be collected by the nurse, using a paper-based collection form (see annex 2). After the campaign a list of all clients tested HIV-positive and/or with a positive TB-screening will be created. Based on this list, data managers will visit the health centers 5 weeks after the campaigns and check in the registers, if these clients came to the facility to be enrolled into chronic HIV/AIDS care and/or to bring their sputum for smear-examination. (As mentioned in annex 1, patients who are expected to bring sputum to the facility and who do not appear at the facility within 5 days have to be traced immediately – bringing sputum after 5 days (through tracing or not) is considered as a negative outcome in the analysis).

Based on information of HTC- and pre-ART/ART-registers, data managers will collect data on absolute numbers newly tested HIV-positive and newly enrolled in chronic HIV/AIDS care during the 4 weeks after the campaigns from each cluster.

Data will subsequently be entered into an EpiData 3.1® database, using double-entry in order to ensure accuracy of data. On the paper records the patient-names appear (as they are needed to verify if the patient came for further care at the facility). However, the names are replaced by a code-identifier before being entered for analysis. The electronic database does not contain any patient-names. The paper-records are stored in locked cupboards at the two SolidarMed site-offices.

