## OBJECTIVES OF THE STUDY

1. Main objective
   1. To compare door-to-door versus pitso in terms of:
      1. HTC-uptake
      2. Newly tested HIV-positive persons
      3. Enrollment into chronic HIV/AIDS care (pre-ART or ART) among newly tested HIV-positive persons
2. Secondary objectives
   1. To compare door-to-door versus pitso in terms of
      1. Proportion of first-time testers
      2. Patient-characteristics (age, sex, first-time tester)
      3. Average CD4-count among clients newly tested HIV-positive
      4. Clinical WHO-stage among clients newly tested HIV-positive
      5. Uptake of other services provided
         1. Blood-pressure measurement
         2. Blood-glucose measurement
         3. Family Planning
         4. Immunization
         5. Deworming
         6. Vitamin A
      6. Detection of Tuberculosis suspects
      7. Sputum turn-around of Tuberculosis suspects
      8. Sputum-results of Tuberculosis suspects
   2. To assess among the clients participating in the study the rate of:
      1. High Random Glucose
      2. High Blood Pressure
      3. Undernutrition/Obesity

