### Procedures

The procedures are defined in the Standard of Procedures (SOP) manual (see annex 1). Study-team-members have been instructed on the SOPs and conducted 4 pre-test campaigns under supervision. The pre-test villages belong to catchment areas that are not part of the study.

In case the team encounters severely ill clients with danger signs, the patients will be transported in the study-car to the hospital (Seboche or Paray hospital), see annex 1.

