## Outcomes measured

### Sources of outcomes

Sources of the different outcomes measured are the study-questionnaire (see annex 2), and the following official registers at the health centers: HTC-register, pre-ART register, ART-register, tuberculosis-suspect register

| *Outcome variable* | *Hypothesis* | *Source/Measure* | *Statistical Method* |
| --- | --- | --- | --- |
| **Primary outcomes** |  |  |  |
| 1. Proportion and absolute number of clients accepting HTC | Higher in door-to-door | Source: study-questionnaire | logistic regression |
| 1. Proportion and absolute number newly tested HIV-positive | Higher in door-to-door | Source: HIV-test result from Determine® & Double Check® (according national guidelines) [binary/count] | logistic regression |
| 1. Proportion and absolute number newly enrolled on chronic HIV/AIDS care within one month after the campaign of those newly tested during campaign | Higher in door-to-door | Source: study-questionnaire and pre-ART and ART-Registers. Enrolled (Y/N) [binary/count] | logistic regression |

| **Secondary outcomes** |  |  |  |
| --- | --- | --- | --- |
| 1. Proportion of first-time testers | Higher in door-to-door | Study-questionnaire [binary] | logistic regression |
| 1. Age of clients attending HTC | Lower in door-to-door | Study-questionnaire [cont] | t-test/ranksum test |
| 1. Sex of clients attending HTC | Proportion of male testers is higher in door-to-door | Study-questionnaire [binary] | logistic regression |
| 1. Proportion newly tested HIV-positive with advanced disease (WHO-stage 3 or 4) | - | Study-questionnaire [binary] | logistic regression |
| 1. Average CD4-count of clients newly tested HIV-positive | - | On-site CD4-count using PIMA^TM^ [cont] | t-test/ranksum-test |
| 1. Absolute number and proportion of clients screened positive for tuberculosis | - | Study-questionnaire [count/binary] | logistic regression |
| 1. Absolute number and proportion of clients positively screened for tuberculosis who bring their sputum to the facility within ≤ 5 days | - | Study-questionnaire and tuberculosis-suspect register | logistic regression |
| 1. Absolute number and proportion of clients bringing their sputum bottles who have a positive direct sputum smear | - | Study-questionnaire and tuberculosis-suspect register | logistic regression |
|  |  |  |  |

Table 2 Primary and secondary outcomes measured in the study

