# Annex 1: Standards of procedures

**Standard Operation Procedures for HTC-campaigns**

- fill-in a file for each client approached for the provision of services
- follow the order of services provided as outlined below

| **Number** | Consecutive numbering. Each team starts every day at 1 |
| --- | --- |
| **Name** | Write Full Name |
| **Resident in CA?** | If the client is resident in the catchment area of the health center where the campaign takes place 🡪 tick Yes |
| **Blood Pressure** | Provide this service to all patients >18 years and write measured blood-pressure into the case. For children 🡪 leave empty.  If blood-pressure ≥140/90 mmHg 🡪 refer to health center for follow-up |
| **HTC accepted** | Propose HTC to all clients (independent of age) who are not already confirmed HIV-positive. All clients agreeing to HTC must fill out the national HTC-consent form!   - if client accepts HTC 🡪 tick “Yes” - if client does not accept HTC 🡪 tick “No” - if client states to be HIV-positive 🡪 tick “ICDP” - if it is a child < 12 years without her/his care-taker 🡪 tick “no guard” - if client is currently in the window-period (<3months since last HIV-test, as confirmed in bukana) 🡪 tick “window”   In case of children < 18 months with a positive HIV-antibody test, the care-taker must be counselled to seek care at the health center for a PCR-confirmation test. |
| **1^st^ time tester** | - if client states that he has never tested before 🡪 tick “Yes” - if client states that he once tested before 🡪 tick “No” - if client is not tested for any reason 🡪 tick “NA” |
| **Test result** | Copy result from test: Positive or Negative or Indeterminate  If the test is positive, the national HTC referral form must be filled out. A list of all newly patients tested positive must be provided to the health center. Patients who do not appear at the health center within 1 month must be traced by the health center (using the SolidarMed tracing fund) |
| **WHO-stage** | Stage all clients with a positive HIV-test according to WHO-staging (see annex) |
| **CD4-count** | Perform CD4-count (PIMA) to all clients who test HIV-positive and note the count in the field. |
| **Height/Weight** | Put height in cm and weight in kg |

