**Outcomes (leave empty, except if already registered icdp)**

| **Brought sputum** | | **Sputum-result** | | **Enrolled on pre-ART** | | **Enrolled on ART** | | **Pre-ART** | **ART-Nb** |
| --- | --- | --- | --- | --- | --- | --- | --- | --- | --- |
| ⬜ Y | ⬜ N | ⬜ Neg | ⬜ Pos | ⬜ Y | ⬜ N | ⬜ Y | ⬜ N |  |  |

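### Enrolment (primary outcome 3) is defined at one month but read at five weeks with no date recorded and from health-centre registers only, so late enrolments can count as successes and hospital enrolments as failures

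*Protocol*

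**What the plan says.** **Definition.** Table 2 of the Protocol (Outcomes measured) defines primary outcome 3 as the proportion and number "newly enrolled on chronic HIV/AIDS care within one month after the campaign of those newly tested during campaign". Its source entry reads "Source: study-questionnaire and pre-ART and ART-Registers. Enrolled (Y/N) [binary/count". The registers named are "the following official registers at the health centers: HTC-register, pre-ART register, ART-register, tuberculosis-suspect register".

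**Variables.** A one-month version of the enrolment variable is listed under Variables collected during testing-campaigns, when it cannot yet be known. The version listed under Variables collected 5 weeks after the campaign is a yes/no with no time limit.

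**Collection.** Under Collection and processing of data, "data managers will visit the health centers 5 weeks after the campaigns and check in the registers". The same section takes cluster-level counts of new enrolments over 4 weeks. It also states that sputum brought after its 5-day limit is a negative outcome, whether or not tracing produced it. It has no matching sentence for enrolment.

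**Tracing.** Annex 1, Test result row: "Patients who do not appear at the health center within 1 month must be traced by the health center".

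**Form.** The outcome block of Annex 2, headed "Outcomes (leave empty, except if already registered icdp", has yes/no boxes for pre-ART and ART and space for the two registration numbers. It has no field for enrolment date or facility.

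**Hospitals.** Study setting says that ART is offered routinely at the hospitals as well as the health centres. Under Procedures, for severely ill clients with danger signs, "the patients will be transported in the study-car to the hospital".

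**The concern.** The outcome has a time limit that the data collected cannot demonstrate. A yes recorded at five weeks does not show whether the client enrolled inside or outside the month. The uncertain days are also not ordinary ones: the health centre's obligation to trace begins at one month, so enrolments may be actively generated just before the registers are read.

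The search also covers only one of the two kinds of facility where a client can start care. A client taken to hospital and enrolled there would appear as not enrolled in the health-centre register.

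Both faults affect how a primary outcome is classified. A later analysis plan could not repair them, because a date or a hospital entry that was never collected cannot be recovered at analysis.

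**Working it through.** **The plan's own figure.** The protocol gives no expected enrolment rate. Its only design calculation is for HTC uptake: 80% against 65%, k = 0.1, 200 clients per cluster, 80% power, 5% significance (taken as two-sided). The unmatched Hayes and Bennett formula gives

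c = 1 + (1.96 + 0.84)² × [0.65×0.35/200 + 0.80×0.20/200 + 0.1²×(0.65² + 0.80²)] / 0.15² = 5.38,

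which rounds up to the stated 6 clusters per arm. This reproduces the plan but has no bearing on the present point.

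**Windows side by side.**

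| Place in the Protocol | Window for enrolment |
| --- | --- |
| Table 2, primary outcome 3 | one month |
| Variables collected during testing-campaigns | 1 month |
| Variables collected 5 weeks after the campaign | none stated |
| Collection and processing of data, individual clients | registers read at 5 weeks |
| Collection and processing of data, cluster counts | 4 weeks |
| Annex 1, start of tracing | after 1 month |
| Annex 2, form | no date field |

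**Length of the gap.** Five weeks is 35 days. Counting both periods from the same day, 35 − 31 = 4 and 35 − 28 = 7, so the gap is 4 to 7 days.

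**Direction and possible size.** Let t be the true one-month enrolment proportion, L the share of the remainder who enrol between one month and five weeks, and h the share of enrolments made at hospital and not found. Then

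observed = (1 − h) × [t + (1 − t) × L].

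All three values are assumptions; the documents give none of them.

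| t | L = 5% to 20%, h = 0 | L = 0, h = 5% to 20% |
| --- | --- | --- |
| 30% | 33.5% to 44% | 28.5% to 24% |
| 50% | 52.5% to 60% | 47.5% to 40% |

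The errors can nearly cancel: t = 30%, L = 10%, h = 20% gives 0.8 × (0.30 + 0.70 × 0.10) = 29.6%. Nothing in the plan makes them do so.

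**Effect on the comparison.** If L and h are the same in both arms, the observed difference is (1 − h)(1 − L) times the true one. With L = h = 10% the factor is 0.9 × 0.9 = 0.81: true values of 50% and 30% are read as 49.5% and 33.3%, a difference of 16.2 points instead of 20. If L or h differs between arms, the bias can go either way.

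**The case against.** The strongest reply is that the window is already fixed. Table 2 and the campaign variable list both say one month, so an enrolment after that is negative by definition, traced or not. Reading registers after the window has closed is normal practice. The 4-week cluster counts are workable only if register entries can be dated, so a careful data manager could apply the limit. The sputum field on the form is an undated yes/no as well.

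Much of this stands. A reader might infer that the outcome has no time limit or that late enrolments are counted by design; the documents do not support that. What remains is that the variable collected at five weeks omits the limit (its sputum counterpart on the same list carries one) and that nothing requires or records the check.

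On hospitals, the intended pathway is the health centre, which receives the list of positives and traces them, and transport is only for the severely ill. This limits the number missed but does not remove the gap.

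Three further inferences are tempting:

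- **That earlier registrations are generally scored as new enrolments.** Known positives are excluded from the primary outcomes under Exclusion criteria, the form has a box for them (ICDP), and its outcome block is to be completed for those already registered. Only clients who do not disclose their status remain, because the box rests on what they state. They are in the first place an issue for outcome 2.
- **That the denominator is contradictory.** Table 2 refers to those newly tested, but the objectives specify "Enrollment into chronic HIV/AIDS care (pre-ART or ART) among newly tested HIV-positive persons" and the follow-up list is built from clients who tested positive. The Table 2 wording is shorthand.
- **That the bias can be given in percentage points, or shown to differ between home and tent.** The documents state no yield of new positives and no late, hospital or concealment rate.

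**Conclusion.** The point holds as a weakness in how primary outcome 3 is ascertained, and it should be corrected. Followed as written, the plan can count enrolments from a 4 to 7 day gap as successes, contrary to its own definition, and can count hospital enrolments as failures. The correct statement is that clients can be misclassified, not that they are. The gap length assumes that one month and five weeks run from the same day. The ranges under assumed rates show direction and plausible scale only; the net error and any difference between arms are unknown.

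**What to change.** - Add two fields to the Annex 2 outcome block: enrolment date and enrolling facility, both copied from the register.
- State one window in days, counted from a named day, and use it in Table 2, in both variable lists and in Collection and processing of data.
- Say that enrolment after that window, traced or not, is scored as not enrolled, in parallel with the existing sputum rule.
- Name the pre-ART and ART registers of the two hospitals as a source and search them for every client on the list of positives.
- As a minor addition, where the recorded date shows registration before the campaign, treat the client as already known HIV-positive under the existing exclusion from the primary outcomes.

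The cost is two form fields and a name search at two hospitals. The hospital search is a small addition to the health-centre visits, since the protocol does not show data managers visiting the hospitals at present. The paper records already carry the names needed. Tracing and transport of patients need not change; only the recording and scoring do.

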## Statistical Analysis

All primary outcomes are binary variables. Absolute counts and proportions will be reported. To assess differences in primary outcomes, adjusted logistic regression will be used. All logistic regression models will be adjusted for clustering using the cl-command in STATA.

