## Hypothesis

In comparison to the traditional “Pitso”-approach (community gathering), the door-to-door approach will result in a higher uptake of HTC, more newly detected HIV-positive persons and more patients newly enrolled into chronic HIV/AIDS-care using the same resources (financial, time and HR). The effect will be measurable as a a higher proportion and absolute number of people being tested HIV-positive, and on a cluster-level (health center) by a higher number of people enrolled in chronic HIV/AIDS care during the month following the campaigns.

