### Individual level

On an individual level, the traditional way of HTC-campaigns (pitso) is a very biased approach as someone has to show up at the pitso in order to get the services. Door-to-door will probably reach other people as compared to pitso. However, it is part of the study-hypothesis that a different population will be reached using door to door. Differences in age and gender for example will be assessed as secondary outcomes. As the pitso is usually held in the center of the village (chief’s place), the door-to-door campaigns also start at the center and move towards the periphery.

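### Absolute numbers are part of every primary outcome, but the analysis treats all three as binary and gives the numbers no inference

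*Protocol*

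**What the plan says.** In the protocol's outcome table (Outcomes measured, Table 2), all three primary outcomes have two components:

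- Outcome 1: "Proportion and absolute number of clients accepting HTC".
- Outcome 2: "Proportion and absolute number newly tested HIV-positive".
- Outcome 3: "Proportion and absolute number newly enrolled on chronic HIV/AIDS care within one month after the campaign of those newly tested during campaign".

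Each is hypothesised to be higher in door-to-door. Outcomes 2 and 3 are typed as both binary and count; the entry for outcome 3 reads "Enrolled (Y/N) [binary/count" before the closing bracket. The method column gives logistic regression for all three.

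The Hypothesis predicts "a higher proportion and absolute number of people being tested HIV-positive" and, at health-centre level, a higher number enrolled in the month after the campaigns, with equal money, time and staff in both arms. Under Collection and processing of data, counts of new positives and new enrolments over the four weeks after the campaigns are taken from the registers for each cluster.

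The Statistical Analysis section says: "All primary outcomes are binary variables". Its next sentence promises that counts will be reported alongside proportions. Differences are to be assessed by adjusted logistic regression with an allowance for clustering. No test, interval or model for a count appears.

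**The concern.** The outcome definitions and the analysis contradict each other. A count per health centre is not a binary variable, and the model chosen for all three outcomes does not address it.

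Logistic regression estimates the odds of accepting, testing positive or enrolling among clients already in the data. How many clients were reached is taken as given. Yet that number is where the two approaches may differ most, and the denominators arise differently. Pitso clients choose to come: the protocol says that "the traditional way of HTC-campaigns (pitso) is a very biased approach as someone has to show up at the pitso" to get the services. Door-to-door clients are those found at home, since empty households are passed over. Because staff, hours and days are the same in both arms (Conduction of campaigns), the number tested, diagnosed or enrolled per campaign is the quantity that most directly answers the equal-resources question, and it needs no arm-dependent denominator.

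At stake is whether the trial can make any inferential statement about absolute numbers, which it announces for every primary outcome.

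**Working it through.** **Inputs.** From Sample size: uptake 80% (door-to-door) and 65% (pitso), k = 0.1, 200 clients per cluster, power 80%, significance level 5% (taken as two-sided, since the protocol does not say), 6 clusters per arm.

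**Step 1: the plan's own figure.** Hayes and Bennett formula for two proportions, unmatched:

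c = 1 + (1.96 + 0.84)² × [p0(1−p0)/m + p1(1−p1)/m + k²(p0² + p1²)] / (p1 − p0)²

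- Bracket: 0.2275/200 + 0.16/200 + 0.01 × (0.4225 + 0.64) = 0.01256.
- Divided by 0.15² = 0.0225 this is 0.558; multiplied by 7.85 it is 4.38.
- c = 5.38, rounded up to 6. The stated figure reproduces. It concerns the uptake proportion only.

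**Step 2: can proportion and number disagree?**

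- With 200 clients in each arm: 0.80 × 200 = 160 and 0.65 × 200 = 130 acceptors. Both components favour door-to-door.
- Numbers are equal when pitso attendance is 0.80/0.65 = 1.23 times door-to-door attendance. With 200 door-to-door clients, 160/0.65 = 246.2, so 247 pitso clients give more acceptors (0.65 × 247 = 160.6).
- Seen from the other side, with 200 pitso clients the ranking reverses once door-to-door serves fewer than 130/0.80 = 162.5. For example, 150 against 200 clients gives 120 against 130 acceptors.

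In each reversed case the proportion still favours door-to-door by 15 points.

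**Step 3: would the planned test show it?** An illustrative simulation assumed mean attendance of 130 (door-to-door) and 200 (pitso) per cluster, uptake 80% and 65%, k = 0.1, 6 clusters per arm and 1000 runs. In 90% of runs the cluster-robust logistic comparison was significant for door-to-door while its total number of acceptors was lower. With a cluster-level t-test on proportions the figure was 83%. The attendance values are assumptions chosen to show the mechanism; they do not say how likely it is.

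**Step 4: what could a count comparison detect?** Hayes and Bennett formula for counts, unmatched, with mean counts L1 = 160 and L0 = 130:

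c = 1 + 7.85 × [(L0 + L1) + k²(L0² + L1²)] / (L1 − L0)²

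| Assumed k for counts | Bracket | Clusters per arm for 80% power | Power with 6 per arm |
|---|---|---|---|
| 0.1 | 290 + 425 = 715 | 7.24, so 8 | 71% |
| 0.2 | 290 + 1700 = 1990 | 18.35, so 19 | 32% |
| 0.3 | 290 + 3825 = 4115 | 36.89, so 37 | 18% |

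The protocol gives k only for the uptake design. A count also varies with attendance, so its k could well be larger; pairing may recover some of that.

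**The case against.** The strongest reply is that counts are not ignored: the protocol says they will be reported, so a reversal in numbers would be visible to any reader. The trial is sized on the uptake proportion, and the logistic comparison of that proportion remains a defined analysis. This stands, and it limits the point to missing inference on counts.

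Three stronger readings are tempting and should not be drawn.

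- A reader might infer that the trial would declare success while its claim about numbers is false. The protocol states no success rule, so this cannot be said. Nor is a fixed share of the hypothesis untested: the Hypothesis pairs proportion with number only for testing positive, gives only a number for enrolment, and speaks simply of higher uptake for testing. The pairing for all three outcomes comes from Table 2.
- A reader might infer that pitso will in fact serve more people. Nothing in the protocol shows this. The pitso arm is also limited, to two tents, the same four health workers and the same hours, and the sample-size section plans 200 per cluster without separating the arms.
- A reader might take the eligibility rule of at least 25 households to mean that household numbers are available for scaling the counts. The rule sets only a minimum, and no household count is among the listed variables or on the questionnaire.

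Leaving the matter to a separate analysis plan does not answer the point, because Table 2 and the Statistical Analysis section both fix the method. A plan that followed them would inherit the contradiction.

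**Conclusion.** The point holds as an internal contradiction that affects all three primary outcomes. The protocol defines and hypothesises absolute numbers, then classes every primary outcome as binary and fixes a method that cannot compare numbers. Counts get description only.

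The break-even ratio of 1.23 follows directly from the planned 80% and 65%. Whether attendance will differ by that much is unknown, and any statement about how often the components would disagree rests on assumed attendance. A formal count comparison may have limited power with six pairs: roughly 71% at an assumed k of 0.1 and 32% at 0.2, for 160 against 130 acceptors and without allowing for the pairing. That is a reason to settle the role of the counts before the analysis.

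**What to change.** Correct the sentence that calls all primary outcomes binary, and the method column of Table 2. Then take one of two routes.

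1. **Test the counts.** For each primary outcome, total the number per health centre over the five campaign days, with the same exclusions as for the proportion (known HIV-positive, tested within 3 months). Compare totals across the six matched pairs, for example by a paired t-test on log totals, and report a rate ratio with its confidence interval. Say beforehand what happens if a total is zero: a small constant or a count model. For the Hypothesis's health-centre-level claim on enrolment, use the four-week register counts. State in advance whether the proportion or the count carries the primary conclusion. A rule that both must agree is not needed.
2. **Make the counts descriptive.** Say so, and reword the Hypothesis and Table 2 so that no superiority in absolute numbers is claimed.

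The cost is mainly wording. Campaign totals come from the forms completed for each client and the existing five-week register check, and the register counts are already planned, so no new data are needed. The price of the first route is the limited power shown above, which should be acknowledged in the plan.

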## STUDY DESIGN

Prospective cluster-randomized study. Each health center within the SMART project area (n=12) with its catchment area represents a cluster. One study arm provides integrated HTC using the door-to-door approach (6 HCs) as compared to the other arm using the pitso-approach (6 HCs)

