## Randomization and allocation

### Clusters and sub-clusters

One Health Center with its catchment area forms a cluster. There are 12 Health Centers participating in the study, resulting in 6 Clusters per arm. The interventions (HTC-campains) will be held in 5 sub-clusters (villages) each.

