### Randomization

The 12 health centers were openly randomized into two equal groups. Before randomization, clusters were stratified and paired according to their average-numbers of monthly new HIV-positive tested clients at routine clinic-based HTC (routine data from October to December 2010).

During an official meeting held on October the 3rd, a person not involved in the study threw a coin for one health center in each pair to allocate it either to the door-to-door or the pitso-arm. The other health center in the pair then automatically fell into the other arm. Table 1 shows the cluster-pairs and their allocation:

| **Pitso-arm** | **Door-to-Door arm** | **Time-frame of campaign** |
| --- | --- | --- |
| St Theresa HC (Paray) | St Peters HC (Seboche) | 17.-21. October 2011 |
| Ngoajane HC (Seboche) | Sehong Hong HC (Paray) | 24.-28. October 2011 |
| Linakeng HC (Paray) | Mokoto HC (Paray) | 31.10.-4.11. 2011 |
| Muela HC (Seboche) | Mohlanapeng HC (Paray) | 7.-12. November 2011 |
| Katse HC (Paray) | Boiketsiso HC (Seboche) | 14.-18. November 2011 |
| Khohlonso HC (Seboche) | Makhunoane HC (Seboche) | 21.-25. November 2011 |

Table 1 Matched pairs of clusters (health centers), their allocation to the study-arms and period where campaigns are held.

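### Cluster-robust logistic regression on 12 paired health centres does not control the stated 5% level, and the direction of the error depends on how well the pairing works

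*Protocol*

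**What the plan says.** Under Statistical Analysis the protocol states that "To assess differences in primary outcomes, adjusted logistic regression will be used" and that "All logistic regression models will be adjusted for clustering using the cl-command in STATA". Table 2 assigns logistic regression to all three primary outcomes (testing uptake, newly positive, enrolled in care) and to most secondary ones. No small-sample correction, t reference or cluster-level test is named, and the covariates behind the word adjusted are not listed.

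The randomised unit is clear. Study Design says "Each health center within the SMART project area (n=12) with its catchment area represents a cluster", and Clusters and sub-clusters says "There are 12 Health Centers participating in the study, resulting in 6 Clusters per arm"; villages are sub-clusters throughout. Under Randomization, "Before randomization, clusters were stratified and paired according to their average-numbers of monthly new HIV-positive tested clients", and a coin was tossed within each of six pairs. The analysis text does not mention the pairs.

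Sample size gives "Power: 80%; Significance level: 5"%, k = 0.1, an uptake difference written as "80% (door-to-door) versus 65% (pitso") and "clients per cluster: 200 (persons attending the services per cluster"), leading to six clusters per arm. The section on selection biases and confounders concedes that the number of clusters is very low, but answers this only with matching.

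**The concern.** A sandwich variance is justified when the number of clusters is large. With 12 clusters it tends to be too small, and 1.96 is too small a critical value: the t quantile is 2.23 on 10 df and 2.57 on 5 df. Both faults push towards too many false positives.

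A third feature pushes the other way. The test treats the arms as independent, although centres were allocated within pairs. If paired centres resemble each other, the true variance of the difference is smaller than the unpaired variance, and the test becomes conservative.

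Which effect wins depends on a within-pair correlation that the protocol does not give. At stake are the p-values and confidence intervals of all three primary outcomes and of every secondary outcome analysed by the same model.

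**Working it through.** **Inputs from the protocol.** Two arms of six health centres, six pairs, p0 = 0.65, p1 = 0.80, m = 200, k = 0.1, level 5% (sidedness not stated; two-sided used), power 80%. **Assumed, because not given:** within-pair correlation 0, 0.3 or 0.6 (latent normal scale); cluster-size CV 0 or 0.4.

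**1. The plan's own figure.** Unmatched Hayes-Bennett formula:

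c = 1 + (1.96 + 0.842)² × [p0(1−p0)/m + p1(1−p1)/m + k²(p0² + p1²)] / (p0 − p1)²

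- Bracket: 0.0011375 + 0.0008 + 0.010625 = 0.0125625
- Divided by 0.15² = 0.0225: 0.5583
- Multiplied by 7.849: 4.38
- c = 5.38, rounded up to 6. The stated six per arm is reproduced; formula power at six is 84.9%.
- The matched version adds 2 instead of 1: 6.38, rounded up to 7; formula power at six is 76.3%.

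So the sample size was computed as if the trial were unmatched.

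**2. Why the level moves (equal cluster sizes, unrelated pairs).** Let SS be the sum of squared deviations of the 12 cluster proportions from their arm means.

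- Robust variance with the 12/11 factor: (SS/36) × (12/11) = SS/33
- Variance in the two-sample t-test: (SS/10) × (2/6) = SS/30

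To this approximation the robust statistic is √(33/30) = 1.049 times a t statistic on 10 df. It exceeds 1.96 when |t| > 1.96/1.049 = 1.87, which has probability 9.1%. With a t reference on 10 df but the same variance, the cut-off is 2.228/1.049 = 2.12, with probability 6.0%. Both the reference and the variance therefore contribute.

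**3. Simulation under the null.** Beta-distributed cluster proportions, closed-form logistic sandwich variance with factor 12/11, cut-off 1.96, 100,000 trials per scenario, uptake 65% and 80%:

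| Within-pair correlation | Equal sizes | Size CV 0.4 |
|---|---|---|
| 0 | 9.0-9.3% | 10.5-10.9% |
| 0.3 | 5.7-5.8% | 7.0-7.4% |
| 0.6 | 2.6-3.0% | 3.8-4.2% |

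The first cell agrees with the 9.1% of step 2. In the same setting a paired t-test on cluster proportions (5 df) stays at about 5% throughout (4.8-5.1%). An unpaired cluster-level t-test (10 df) gives about 5% at correlation 0, about 3% at 0.3 and about 1% at 0.6.

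**4. Other primary outcomes (rates assumed).** Newly positive at 3-10%, 150 clients per cluster, k 0.25-0.5, size CV 0.4: 9.9-11.0% at correlation 0 and 7.7-8.9% at 0.3. Enrolment at 30-50% with about 10 positives per cluster, unrelated pairs: 9.0-9.1%.

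**5. Adding pair indicators to the planned model is not a remedy.** With centre-level robust errors, and D the sum of squared deviations of the six differences from their mean, the robust variance is (D/72) × (12/11) = D/66, against D/30 for the paired t-test. The cut-off in t units on 5 df is 1.96/√(66/30) = 1.32, with probability 24%. Simulation also gives about 24% at each correlation tried.

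**6. Power for 65% versus 80%, equal sizes.**

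| Within-pair correlation | Paired t (5 df) | Unpaired cluster-level t (10 df) |
|---|---|---|
| 0 | 74% | about 82% |
| 0.3 | 84% | 85% |
| 0.6 | 94% | 87% |

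**The case against.** The strongest reply is that the trial is matched, and matching offsets the fault. At a correlation of 0.4 the planned test rejects 4.5-4.6% with equal cluster sizes and 6.0-6.1% with size CV 0.4, which is close to nominal. This stands, and it rules out a tempting stronger reading: that the false-positive rate is simply doubled and a significant door-to-door advantage would be an artefact of standard errors that are too small. The documents do not support a one-directional claim. Nor do they support relying on the matching. No correlation is given. Randomization names one pairing variable (monthly new positives), while the section on selection biases lists three. Four of the six pairs in Table 1 join a Paray centre with a Seboche centre.

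A reader might also infer that the clustering level is open, so that the 60 villages (12 × 5) could be used as clusters. The text does not support this: Study Design and Clusters and sub-clusters both make the health centre the cluster.

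Two further points stand in part. The simulated model is unadjusted, while the plan adjusts for unnamed covariates, so the exact percentages are illustrative. A separate analysis plan could add a correction; but the protocol does not leave the method open, and the method it names does not hold the level.

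**Conclusion.** The concern holds in this form: the planned primary analysis does not control the stated 5% level. For uptake, the outcome on which the trial is sized, the actual level of the unadjusted test runs from about 2.5% to about 11% over the assumed correlations of 0 to 0.6 and size CVs of 0 to 0.4. It is about 9% at the protocol's own k and cluster size if pairing is uninformative and sizes are equal. The result rests on reading the cl-command as Stata's cluster option at health-centre level with a normal reference, and on a two-sided test. Figures for the second and third primary outcomes rest on assumed rates; the point does not need them. Because every primary p-value and interval depends on this choice, and the remedy needs no new data, it should be changed before analysis.

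**What to change.** In Statistical Analysis and Table 2, replace the confirmatory test for the primary outcomes with one that is valid for few clusters, at the health-centre level already defined.

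- **Preferred, because it respects the pairing:** compute the outcome proportion in each of the 12 centres, take the six within-pair differences, and report a paired t-test (5 df) with its confidence interval.
- **Acceptable alternatives:** an unpaired cluster-level t-test (10 df), which is conservative if pairing is informative, or a small-sample-corrected robust variance with a t reference. A t reference alone is not enough: with the uncorrected variance at 80% uptake and unrelated pairs it still rejects 6.0% (7.3% at size CV 0.4).
- **Keep** logistic regression for adjusted odds ratios, with the corrected variance and with covariates named.

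The cost is wording, wider intervals and some power. The paired test falls below the planned 80% if pairs are unrelated (74%) and exceeds it at correlation 0.3 or more; the unpaired cluster-level test stays at about 82-87%. Sample size should restate power for the chosen test and say whether the matched or unmatched formula applies, since six per arm follows only from the unmatched one.
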